#### Women With Moderate Vitamin D Deficiency (Group B)

Group B1: Subjects were treated with 50,000 IU oral vitD3 weekly for a total duration of 6 weeks.

Group B2: Subjects were treated with 50,000 IU oral vitD3 weekly for a total duration of 6 weeks and then were on monthly maintenance dose of 50,000 IU vitD3 until delivery.

GroupB3: Subjects were treated with a single dose of intramuscular administration of 300,000 IU vitD3.

GroupA4: Subjects were treated with a single dose of Intramuscular administration of 300,000 IU vitD3 and then were on monthly maintenance dose of 50,000 IU vitD3 until delivery.

Participants were advised to inform the health care provider about any adverse side effect. A fasting blood sample was obtained 3 months after termination of the intervention for those without maintenance vitamin D therapy (groups A1, A3, B1, and B3) and for all those in other groups at delivery. Also, a cord blood sample was obtained from participants. Separated serum samples after centrifugation were transferred to the central laboratory of Masjed-Soleyman. Samples were stored at −80°C and serum concentrations of vitamin D3 were measured at the end of the study.

#### Women With Normal Status (Group C)

Subjects in this group and the pregnant women recruited from Shushtar city comprised our controls. They had access to standard prenatal care and were followed until delivery. In the case of any adverse outcome, it was managed according to the perinatal guidelines. Blood sampling from subjects in this group and those from Shushtar was obtained at the first visit. Similar to others groups, another sample was obtained from mothers and umbilical cord at the time of delivery.

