### Clinical Endpoints

Primary endpoints are to find out the beneficiary impact of screening of pregnant women for vitamin D deficiency on pregnancy and neonatal outcomes and assessing the effect of supplementation with vitamin D on these outcomes. In the screening group, within the framework of randomized controlled trial, the endpoint was cord serum concentration of 25(OH)D to compare various doses, regimen, and routes for vitamin D supplementation in pregnancy.

In this regard, primary outcomes are gestational diabetes, preterm delivery, and pregnancy induced hypertension. Secondary outcomes are type of delivery and neonatal outcomes including birth weight (gr); head circumference (cm), height (cm); appearance, pulse, grimace, activity, respiration (APGAR) score 1, 5 minute, icterus, cord falling off time (day), serum calcium concentration (mg/dl), and cord levels of 25(OH)D (ng/ml).

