### Research Questions

The questions are as follows: (1) How is the status of vitamin D among pregnant women in Khuzestan? (2) Is vitamin D deficiency related to adverse maternal and neonatal outcomes in pregnancy? (3) Does supplementation with vitamin D improve maternal and neonatal outcomes? (4) Is there any difference between various doses, regimen, and route for vitamin D supplementation in terms of pregnancy outcomes? (5) Taken altogether, is it reasonable to advise universal vitamin D deficiency screening program to detect and treat vitamin D deficiency in pregnancy?

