## Methods

### Overall Study Design

This was a 2-phase population-based study. The first phase comprised a population-based cross-sectional study in which 1600 and 900 first trimester pregnant women attending health centers of Masjed-Soleyman and Shushtar, Khuzestan province, Iran were recruited using stratified multistage cluster sampling with probability proportional to size (PPS) method [33]. In the second phase of this study, within the framework of screening regimen, Masjed-Soleyman participants with vitamin D deficiency were assigned to a screening program versus Shushtar participants (as nonscreening arm) to assess the effectiveness of various treatment regimens. Pregnancy outcomes including preterm delivery, miscarriage, preeclampsia, gestational diabetes, and type of delivery and neonatal outcomes including birth weight (gr), head circumference (cm), height (cm), APGAR score 1, 5 minute, icterus, cord falling off time (day), serum calcium (mg/dl) level, and cord concentration of 25(OH)D (ng/ml) were recorded.

Shushtar participants (as nonscreening arm) served as controls and were followed till delivery and any adverse pregnancy outcomes were assessed.

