### Blood Assessments

Upon enrollment into the study, a fasting blood sample was obtained from all participants. Separated serum samples by centrifugation were transferred to the central laboratory of Masjed-Soleyman (cold chain was kept during storage and transfer processes). The serum samples of participants in Shushtar were stored and kept frozen at -80°C until assayed at the end of the study, but at that time the serum concentration of vitamin D of Masjed-Soleyman participants were promptly measured. Based on 25(OH)D levels, mothers were divided as severe deficient (<10ng/ml), moderate deficient (10-20ng/ml), and normal status (>20ng/ml) [1]. The scale to express 25(OH)D status results was according to ng/ml; each 1 ng/ml is equal to 2.496 nmol/L.

Those participants from Shushtar and those with serum vitamin D>20 ng/ml from Masjed-Soleyman served as controls and were followed until delivery. Subjects with severe and moderate vitamin D deficiency from Masjed-Soleyman were selected for the second phase of the study and were randomly allocated to one of the treatment modalities presented in Figure 1.

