### The Second Phase

In the second phase of the study, to assess the effect of screening strategy on maternal and neonatal outcomes, Masjed-Soleyman participants were assigned to a screening program versus Shushtar participants acting as the nonscreening arm. Within the framework of the screening regimen, an 8-arm blind randomized clinical trial was undertaken to compare the effects of various treatment protocols. Due to the cost and complexity of the process, 800 pregnant women with vitamin D deficiency from Masjed-Soleyman were randomly allocated to 1 of the designed intervention programs according to the study Figure 1. The remaining women with vitamin D deficiency were referred to specialists for further treatments. Participants of Shushtar did not receive any vitamin D supplementation. However, the comparison of the basic confounders between the initial recruited sample in Masjed-Solayman and the women allocated to intervention indicated no statistically significant difference and hence no selection bias occurred during the allocation of treatment (Table 4).

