### Statistical Analysis

Data will be expressed as mean (standard deviation, SD) for normally distributed variables and frequency (%) or median (interquartile range, IQR) for categorical and or nonnormal variables. Continuous variables are checked for normality using the one sample Kolmogorov-Smirnov test. Distribution of variables between the 2 groups is compared using *t* test or Mann-Whitney nonparametric test in case of normality violation and reported as mean (SD). Categorical variables are compared using Pearson and chi-square tests. An intention-to-treat analysis of the results is used. Generalized linear models will be used to assess the relationships between outcomes and exposures (here vitamin D3 supplementation intervention) adjusted by appropriate covariates. Analyses will be performed using the software SPSS version 19 (SPSS Inc). *P* value of less than .05 is considered as significance level.

**Table 1 table1:** The steps of study analysis.

Proceedings		Stage
Obtaining written inform consent form and completing the questionnaire		Recruitment and completion of the questionnaire
Determining groups according to their status of vitamin DCollection of the laboratory samples Obtaining fasting blood samples. Assessment of serum concentration of vitamin D in Masjed-Solayman immediately and storing Shustar samples at −80°C		Classification
Obtaining fasting blood samples 3 months after termination of the intervention for those without maintenance vitamin D therapy (groups A1, A3, B1, and B3) and for all women at delivery time. Obtaining cord blood sample from all participantsStart of intervention Prescription of vitamin D according to various protocols (A1-3 and B1-3) for intervention groups		Replication of laboratory samples
Follow-up of pregnancy outcomes and neonatal calcium and vitamin D status		Follow-up
	
	

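### The comparator for the supplementation aim is not fixed consistently, and the declared controls include women who were never deficient, which would attenuate the effect if they are pooled unstratified

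*Protocol article*

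**What the plan says.** Clinical Endpoints lists "assessing the effect of supplementation with vitamin D on these outcomes" beside the screening effect as a primary endpoint. Research Questions repeats it as question 3: "Does supplementation with vitamin D improve maternal and neonatal outcomes".

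The two Intervention subsections describe four regimens for severe and four for moderate deficiency. All eight contain vitamin D3. The Second Phase covers the deficient Masjed-Soleyman women who were not randomised: "The remaining women with vitamin D deficiency were referred to specialists for further treatments". On the other city it says: "Participants of Shushtar did not receive any vitamin D supplementation".

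The controls are described in three places:

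- Blood Assessments: "Those participants from Shushtar and those with serum vitamin D>20 ng/ml from Masjed-Soleyman served as controls and were followed until delivery".
- Women With Normal Status (Group C): "Subjects in this group and the pregnant women recruited from Shushtar city comprised our controls".
- Overall Study Design: "Shushtar participants (as nonscreening arm) served as controls and were followed till delivery", with no mention of Group C.

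The Abstract and The Second Phase also place the Masjed-Soleyman participants in the screening programme without excepting those of normal status, so Group C is described both as part of the screening arm and as control.

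Statistical Analysis states: "Generalized linear models will be used to assess the relationships between outcomes and exposures (here vitamin D3 supplementation intervention"), with adjustment for covariates it does not name. It does not define the unexposed group or restrict the comparison to deficient women.

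**The concern.** Question 3 asks what would have happened to deficient women without supplementation. Masjed-Soleyman cannot supply that group: its deficient women were either randomised to an active regimen or referred for treatment. Within that city, being supplemented in the trial and being deficient at baseline coincide.

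The declared controls answer the question only in part. Most Shushtar women are deficient and untreated, but some are above 20 ng/ml, and all of Group C is. If deficiency raises the risk of adverse outcomes, women above 20 ng/ml have a lower untreated risk than the treated women would have had. Including them lowers the control risk and makes supplementation look less useful than it is.

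Baseline adjustment cannot repair the Group C part. Treated women are at or below 20 ng/ml and Group C is above it, so there is no overlap in baseline 25(OH)D on which to adjust.

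**Working it through.** The protocol gives no figure for a supplemented-versus-unsupplemented contrast, so there is none to reproduce. The check estimates how much of the control pool was never deficient and what that does to a risk difference.

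**Inputs from the document.** Shushtar 25(OH)D: median 11 (IQR 7-16) ng/ml, n=900 (Table 2). Masjed-Soleyman initial sample: 11.9 (8-17), n=1581 (Table 4). Randomised: 800.

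**Assumptions.** The distribution is log-normal or normal. Group C is either every initial-sample woman above 20 ng/ml, or 100 women. The 100 is the 900 Masjed-Soleyman women in Table 2 minus 800 randomised; it is only a guess, because Table 4 labels 900 as allocated to intervention.

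**Step 1: share above 20 ng/ml.**

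- Log-normal, SD of log = ln(Q3/Q1)/1.349. Shushtar: ln(16/7)/1.349 = 0.613; P = 1 - Φ(ln(20/11)/0.613) = 16.5%, 148 women. Masjed-Soleyman: ln(17/8)/1.349 = 0.559; P = 1 - Φ(ln(20/11.9)/0.559) = 17.6%, 279 women.
- Normal, SD = (Q3 - Q1)/1.349 = 9/1.349 = 6.67 in both. Shushtar: 1 - Φ(9/6.67) = 8.9%, 80 women. Masjed-Soleyman: 1 - Φ(8.1/6.67) = 11.2%, 178 women.
- Both upper quartiles lie below 20, so neither share can exceed 25%.

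**Step 2: never-deficient share s of the controls.**

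| Controls | Normal | Log-normal |
|---|---|---|
| Shushtar + Group C of 100 | 180/1000 = 18% | 248/1000 = 25% |
| Shushtar + all Masjed-Soleyman women above 20 | 258/1078 = 24% | 427/1179 = 36% |
| Shushtar only | 9% | 16% |

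The quartile bound is (225 + 395)/(900 + 395) = 48%.

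**Step 3: effect on the estimate.** Let D be the excess risk of untreated deficiency and f the fraction of it that treatment removes. The true risk difference is -fD. Against the unstratified pool it is -(f - s)D. The estimate moves towards harm by sD: a proportional loss of s/f, equal to s when f = 1 and larger when f is smaller. The sign changes only if f < s.

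**Step 4: illustration**, with assumed risks of 15% (untreated deficient) and 10% (sufficient), so D = 5 points:

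| f | True difference | s = 0.25 | s = 0.36 |
|---|---|---|---|
| 1 | -5.0 | -3.75 | -3.2 |
| 0.5 | -2.5 | -1.25 | -0.7 |
| 0.2 | -1.0 | +0.25 | +0.8 |
| 0 | 0 | +1.25 | +1.8 |

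At f = 1, 800 treated women have about 85% power (two-sided 5%, assumed) against 752 deficient Shushtar women, and about 68% against a pool of 1000 with s = 0.25. Clustering and city differences are ignored.

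**Step 5: is a better comparator available?** Yes. Data Collection and Quality Control Procedures says the stored Shushtar samples were assayed at the end of the study, and Table 2 reports the values. Shushtar women at or below 20 ng/ml number 900 - 148 = 752 (log-normal) to 900 - 80 = 820 (normal), and at least 675 by the quartile bound. Below 10 ng/ml: 900 × Φ(ln(10/11)/0.613) ≈ 394, or 900 × Φ(-1/6.67) ≈ 396. That leaves about 358 to 424 at 10-20 ng/ml.

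**The case against.** The strongest reply is that the biased estimator is not in the text. No section says that treated women will be compared with Group C and Shushtar merged and unstratified. Calling both groups controls also fits two separate reference groups, one untreated and one of normal status. A reader might infer that the supplementation estimate is diluted or even reversed; the document supports only that it would be if the declared pool were used as it stands. That part of the objection stands.

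It can also be said that a condensed article leaves comparator subsets and covariates to an analysis plan. This carries weight for the Shushtar contrast, where adjustment or stratification on baseline 25(OH)D is possible. It does not cover Group C, where baseline ranges do not overlap, nor the disagreement between sections over who the controls are.

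Three further limits stand. Whether deficiency is related to adverse outcomes is the trial's own open question 2; if sufficient women have no lower risk, there is no dilution. The size of Group C is not given, so 36% is the upper end of a range and not a single estimate. Reversal of a true benefit is a special case: in the table above it appears only at f = 0.2.

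Finally, a reader might conclude that no usable untreated comparator exists. The deficient Shushtar women are one, though non-randomised.

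**Conclusion.** The point holds in a conditional form. For question 3 the eight active arms supply no randomised untreated contrast, the sections disagree on the controls, and two of them include women who were never deficient. Used unstratified, and if deficiency raises risk, that pool would shrink the effect of a fully effective treatment by about 18-36%, or about 9-16% if Shushtar alone is the control. Treatments that remove only part of the excess risk lose proportionally more, and the sign changes only when that part is smaller than the never-deficient share.

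These sizes rest on an assumed 25(OH)D distribution and an assumed Group C; the point differences also rest on the assumed 15% and 10% risks. The randomised comparison of regimens, with cord 25(OH)D as endpoint, is unaffected. This should be corrected, because the change is small and the data are already collected.

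**What to change.** Reconcile Overall Study Design, Blood Assessments and Women With Normal Status (Group C) on who the controls are, and for which question. For question 3:

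- Compare the A arms with Shushtar women whose baseline 25(OH)D is below 10 ng/ml and the B arms with Shushtar women at 10-20 ng/ml, analysed by severity stratum.
- Exclude Group C and Shushtar women above 20 ng/ml from this comparison.
- Adjust for the baseline factors that differ between the cities in Table 3: sun exposure, cream, gloves, veil, accommodation and spouse education.
- Label the result non-randomised and confounded with city. Restriction removes the dilution, not the city difference.

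Group C against Shushtar women above 20 ng/ml may be reported as an optional negative-control check, since neither group was assigned supplementation. It is imprecise. At 10% risk the main contrast has standard error √(0.09/800 + 0.09/752) = 1.5 points. Subtracting the control contrast raises it to √(0.09/800 + 0.09/752 + 0.09/279 + 0.09/148) = 3.4 points, or 4.2 with 100 in place of 279. It should not be the main estimate.

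The costs are a somewhat smaller comparator (about 752-820 of the 900 Shushtar women) and a comparator fixed late. Results says the study is already at the data analysis stage, so the timing of the choice should be disclosed.

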### Source of Vitamin D

Oral vitamin D3 50 000 U or cholecalciferol tablets were manufactured by Roche Pharmaceutical, Tehran, Iran and dispersed in Iran by Zahravi, Tehran, Iran. Intramuscular D3 injection of 1-ml ampoule, 300 000 IU/ml in sesame oil, was manufactured by Caspian Pharmaceutical, Iran.

### Adherence to Medication Regimen

Adherence to the supplementation regimen was measured by maternal self-report and pill counts at each prenatal visit. The number of pills returned was divided by the expected number of pills that would have been taken to create a percentage that indicates the adherence of medication regimen. The measures were used to make an average adherence for each subject [35].

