#### Women With Severe Vitamin D Deficiency (Group A)

Group A1: Subjects were treated with 50,000 IU of oral vitD3 weekly for a total duration of 12 weeks.

Group A2: Subjects were treated with 50,000 IU of oral vitD3 weekly for a total duration of 12 weeks and then were on monthly maintenance dose of 50,000 IU vitD3 until delivery.

GroupA3: Subjects were treated with intramuscular administration of 300,000 IU vitD3; 2 doses for 6 weeks.

GroupA4: Subjects were treated with Intramuscular administration of 300,000 IU vitD3; 2 doses for 6 weeks and then were on monthly maintenance dose of 50,000 IU vitD3 until delivery.

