### Limitations

However, this study is subject to some limitations. First, conducting the study in urban regions restricts its generalizability to rural areas. Second, some pregnancies may be aborted prior to entering the study and hence it could decrease our power to interpret the results of miscarriage outcome. Third, the potential number of our lost to follow-up cases may be another limitation. Finally, fourth is the concern of vitamin D consumption or lack of adherence to the treatment regimen among the intervention groups.

Overall, the results of this study regarding vitamin D deficiency prevalence and optimal supplementation and treatment methods during pregnancy will empower clinicians with novel recommendations in patient decision-making.

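### The adherence percentage is defined as pills returned over pills expected, which measures non-adherence, so the descriptive adherence score runs backwards

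*Protocol article*

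**What the plan says.** The section Adherence to Medication Regimen names two sources of information: "Adherence to the supplementation regimen was measured by maternal self-report and pill counts at each prenatal visit". It then gives the calculation for the count: "The number of pills returned was divided by the expected number of pills that would have been taken", and says that this was done "to create a percentage that indicates the adherence of medication regimen". The section ends: "The measures were used to make an average adherence for each subject".

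Nothing else in the article subtracts returned from dispensed pills, reverses the scale, or gives *returned* a special meaning. The number of pills dispensed is not stated.

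Adherence comes up once more, as the last of four items under Limitations, which mentions "lack of adherence to the treatment regimen among the intervention groups". The Statistical Analysis section specifies intention to treat and does not refer to adherence.

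**The concern.** In a pill count, what a woman brings back is what she did not swallow. A ratio with returned pills on top therefore rises as intake falls. Labelled as adherence, it ranks women in the wrong order: those who took least appear most adherent.

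What is at stake is how the oral regimens are read. One research question compares doses, regimens and routes. A weekly tablet course depends on the woman taking it, so a reader who sees a difference, or no difference, between oral and intramuscular arms will look to adherence for part of the explanation. The article itself lists poor adherence as a limitation. A reversed score would point the wrong way on both counts. The Results section says that the data are already being analysed, so the formula in use should be checked now.

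**Working it through.** **Inputs**

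- Expected tablets in A1: the arm is described as "Group A1: Subjects were treated with 50,000 IU of oral vitD3 weekly for a total duration of 12 weeks". At one tablet per dose, E = 12.
- Expected tablets in B1: "Group B1: Subjects were treated with 50,000 IU oral vitD3 weekly for a total duration of 6 weeks". At one tablet per dose, E = 6.
- Tablet strength: 50,000 units (Source of Vitamin D), which supports one tablet per dose.
- Tablets dispensed, D: not stated. Assumed equal to E, with a surplus of 2 as the other end of the range.

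The article reports no adherence figure, so there is none to reproduce. What can be checked is how the stated rule behaves.

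**Formulas**

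Let T be tablets taken. Returned tablets are R = D − T.

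- Stated rule: R/E = (D − T)/E.
- Corrected rule: (D − R)/E = T/E.

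In the stated rule T enters with a minus sign. Each tablet taken lowers the score by 1/E, which is 1/12 = 8.3 percentage points in A1 and 1/6 = 16.7 points in B1. This is true for any D.

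**Results**

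| Course | Dispensed | Taken | Returned | Stated rule | Corrected rule |
|---|---|---|---|---|---|
| A1 | 12 | 12 | 0 | 0/12 = 0% | 100% |
| A1 | 12 | 9 | 3 | 3/12 = 25% | 75% |
| A1 | 12 | 6 | 6 | 6/12 = 50% | 50% |
| A1 | 12 | 0 | 12 | 12/12 = 100% | 0% |
| A1 | 14 | 12 | 2 | 2/12 = 16.7% | 100% |
| A1 | 14 | 0 | 14 | 14/12 = 116.7% | 0% |
| B1 | 6 | 6 | 0 | 0/6 = 0% | 100% |
| B1 | 6 | 3 | 3 | 3/6 = 50% | 50% |
| B1 | 6 | 0 | 6 | 6/6 = 100% | 0% |
| B1 | 8 | 6 | 2 | 2/6 = 33.3% | 100% |
| B1 | 8 | 0 | 8 | 8/6 = 133.3% | 0% |

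The 0% and 100% endpoints depend on D = E. The reversal does not. With a surplus the stated score can also exceed 100%, while the corrected score stays on the intended scale.

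**Recovering the right value**

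From the formulas, T/E = D/E − (stated score). If D = E, this is 1 minus the stated score. If D is larger, that shortcut is too low: for a full taker in A1 with two surplus tablets it gives 100% − 16.7% = 83.3% instead of 100%, so D is needed.

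**The case against.** The strongest reply is that this is a slip of the pen, *returned* written for *taken* or a subtraction left out, and that nothing important depends on it. Much of this stands. The document cannot show that the reversed calculation was actually run. Adherence is not a primary or secondary outcome, the analysis is by intention to treat, and no per-protocol set, adherence threshold or adherence-adjusted model is described. What does not stand is leaving the sentence alone: it is the only definition given, it is wrong as written, and a reader cannot tell which calculation lies behind any figure reported.

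Three stronger readings are tempting, and the document does not support them.

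- *Treatment comparisons would be reversed or biased.* No comparison that is described uses the adherence percentage. The Limitations section raises poor adherence as a concern but does not say that this percentage will be used to interpret the arms.
- *Averaging with self-report makes the number meaningless.* If the average were taken over the two methods, with truthful self-report scored as T/E and D = E, every woman would score ½ × [(E − T)/E + T/E] = 50%. But the article does not say whether the average is over methods or over visits, and it does not say how self-report was scored. Averaging over visits is at least as natural a reading; the score would then stay reversed but would not collapse to a constant.
- *Adherence to the injections was not planned for.* A pill count cannot describe the intramuscular doses, but the section does not claim that it does, and self-report is not limited to tablets. How injections were recorded is detail that an article may leave to the full protocol. All that is fair to ask here is that the scope of the percentage be stated.

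**Conclusion.** The point holds as an error in a stated formula: the percentage called adherence measures non-adherence. In a 12-tablet course with dispensed equal to expected, full intake scores 0%, nine tablets 25% (75% in truth) and no intake 100%. With two surplus tablets the range becomes 16.7% to 116.7% in A1 and 33.3% to 133.3% in B1, still reversed.

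The severity is modest. The effect is confined to a descriptive variable and reaches no endpoint, sample size or stated test. It matters because a reversed score would mislead the reading of the oral regimens and of the adherence limitation. The conclusion on direction rests only on returned pills being pills not taken. The exact percentages also assume one tablet per dose and the stated numbers dispensed. Whether the error lies in the wording alone or also in the computed variable cannot be settled from the article.

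**What to change.** 1. Replace the definition with: tablet adherence (%) = (pills dispensed − pills returned) / pills expected × 100.
2. Confirm which calculation was used in the data. If it was the stated one, recompute it: 1 minus the score where dispensed equals expected, and dispensed/expected minus the score otherwise.
3. State that the pill-count percentage applies only to doses given as tablets.

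The cost is one corrected sentence and, if needed, one recoded variable. No design change or new data collection is involved. The one dependency is the number of pills dispensed, which the article does not say was recorded; if it was not, the assumption that it equalled the number expected should be stated beside the result.

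### Adherence is defined as pills returned over pills expected, so the printed percentage falls as intake rises

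*Protocol article*

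**What the plan says.** The Adherence to Medication Regimen section of the Protocol article names two sources: "Adherence to the supplementation regimen was measured by maternal self-report and pill counts at each prenatal visit". It then gives the pill-count formula: "The number of pills returned was divided by the expected number of pills that would have been taken to create a percentage", and describes that percentage as one "that indicates the adherence of medication regimen". It closes with: "The measures were used to make an average adherence for each subject".

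Nothing in the section subtracts the ratio from 100% or the returned pills from the number dispensed, and no other section redefines the measure. The number dispensed is not mentioned.

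The Limitations section lists, as part of its fourth and last item, "lack of adherence to the treatment regimen among the intervention groups". The Statistical Analysis section specifies an intention-to-treat analysis and gives adherence no stated role.

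**The concern.** The numerator, the denominator and the label do not fit together. A returned tablet was not swallowed, so a ratio with returned tablets on top measures non-adherence, yet the text calls it adherence. This is a formula fixed the wrong way round, not a detail left to a fuller document.

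Adherence matters for interpretation here. The trial compares doses, regimens and routes, and some arms rely on women taking weekly tablets while others receive injections. If cord 25(OH)D differs between arms, or fails to differ, uneven tablet-taking is an obvious candidate explanation. With a reversed score the best-adhering oral arm would look the worst, and the explanation would point the wrong way.

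The averaging sentence adds a second difficulty. Self-report would normally rise with intake while the printed pill ratio falls. If the two are averaged, they work against each other.

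**Working it through.** The article reports no adherence figure, so there is none to reproduce. The check is direct arithmetic on the printed rule.

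**Inputs**
- E, tablets expected. For A1: "Group A1: Subjects were treated with 50,000 IU of oral vitD3 weekly for a total duration of 12 weeks", so E = 12. For B1: "Group B1: Subjects were treated with 50,000 IU oral vitD3 weekly for a total duration of 6 weeks", so E = 6. Both assume one 50,000 IU tablet per dose.
- D, tablets dispensed. Not stated, so D = E is taken as the natural case and D > E is also tried.
- a, the true fraction of E taken. Tablets returned are then R = D − aE.

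**Formula as printed**

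Score = R/E = D/E − a. It drops by one percentage point for each percentage point of extra intake, whatever D is.

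| E | D | all taken | half taken | none taken |
|---|---|---|---|---|
| 12 | 12 | 0% | 50% | 100% |
| 6 | 6 | 0% | 50% | 100% |
| 12 | 14 | 16.7% | 66.7% | 116.7% |
| 6 | 8 | 33.3% | 83.3% | 133.3% |

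For example, with E = 6, D = 8 and all 6 taken, R = 2 and 2/6 = 33.3%. With D = E, true adherence of 90% is printed as 100% − 90% = 10%. The 0% score for a full taker therefore needs D = E; the reversal does not. With surplus tablets a non-taker scores above 100%.

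**Conventional formula**

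(D − R)/E = a. All, half or none taken gives 100%, 50% or 0% in every row of the table.

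**If self-report and pill count are averaged**

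Let w be the weight on the pill count, and suppose self-report is a truthful percentage equal to a. Then

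mean = w(D/E − a) + (1 − w)a = w·D/E + (1 − 2w)a.

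- w = 1/2: the mean is D/(2E), the same at every intake. It is 50% when D = E, 58.3% for E = 12 with D = 14, and 66.7% for E = 6 with D = 8.
- w = 1/3, D = E: none, half or all taken gives 33.3%, 50% or 66.7%. The direction is right but the range is squeezed.
- w = 2/3, D = E: none, half or all taken gives 66.7%, 50% or 33.3%. The mean is squeezed and reversed.
- w = 1/2, D = E, every woman claiming 100%: the mean is (1 − a + 1)/2 = 1 − a/2, so none, half or all taken gives 100%, 75% or 50%. The mean is reversed.

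**If the average is over visits only**

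The pill-count score is not pulled towards any middle value. With D = E it stays at 0% for a full taker and 100% for a non-taker.

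**Coverage**

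The pill formula has nothing to count in an arm treated only by injection, for example "GroupB3: Subjects were treated with a single dose of intramuscular administration of 300,000 IU vitD3"; A3 is also described with injections only. That is a separate gap. The reversal concerns the arms that do have tablets.

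**The case against.** The strongest reply is that this is a wording slip in a condensed article. The section cites a source that is not available here, no adherence value is reported, and anyone who saw scores near 0% in arms with good uptake would probably notice. That may be so. The article cannot show what was computed, and for that reason the computation needs checking as well as the sentence. It does not make the printed rule correct.

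A second reply is that no planned analysis uses adherence. This stands. The Statistical Analysis section applies intention to treat and does not name adherence as a covariate, an exclusion rule or an outcome. A reader might infer that the comparison of cord 25(OH)D is itself biased; the documents do not support that.

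A third reply concerns the averaging. It is tempting to conclude that every truthful woman ends at about 50% whatever she took. That needs four conditions the text does not give: averaging across the two methods and not only across visits, equal weights, self-report scored as a truthful percentage, and dispensed equal to expected. The sentence can equally be read as averaging visit-level values, so the cancellation is a conditional risk.

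Nor is the pill ratio the only adherence information, since self-report is collected separately and is not itself reversed. The Limitations section does not present adherence as a leading threat either; it is part of the last of four items.

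**Conclusion.** The pill-count definition is wrong as printed: it measures non-adherence and labels it adherence. The reversal holds for any number of tablets dispensed. The particular scores of 0%, 50% and 100% for full, half and no intake rest on dispensed equalling expected and, in the worked examples, on one tablet per dose.

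Cancellation against self-report follows only if the two sources are averaged together, which the text leaves open. It is complete only with equal weights and truthful self-report, and partial otherwise.

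The consequence is limited to reported adherence and to any interpretation built on it, whether among the oral regimens or between oral and injected ones. The intention-to-treat comparison does not change. It is a definite error of moderate importance.

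**What to change.** Define pill adherence as (pills dispensed minus pills returned) divided by pills expected. Establish which formula was actually applied to the data. If it was the printed one, recompute from the recorded counts; if it was not, correct the text. Recomputation needs the number dispensed to each woman, or confirmation that it equalled the number expected. The article does not say that dispensed counts were kept, so this should be checked first.

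State whether the per-woman average is over visits, over the two methods or both, with what weights, and how self-report is turned into a percentage. Report self-report and pill count separately, or combine them only once both rise with intake. Say also how adherence is recorded for injected doses.

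The cost is one corrected definition, a clarified averaging rule and, if needed, a recomputation. If dispensed counts exist or equalled the number expected, no new data are required. The article reports that the study is at the data-analysis stage, so this should be settled before adherence is reported.
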